## Abstract

**Background:**

Pedometer-based programs have elicited increased walking behaviors associated with improvements in blood pressure in sedentary/low active postmenopausal women, a population at increased risk of cardiovascular disease. Such programs typically encourage increasing the volume of physical activity with little regard for its intensity. Recent advances in commercially available pedometer technology now permit tracking of both steps/day and time in moderate (or greater) intensity physical activity on a daily basis. It is not known whether the dual message to increase steps/day while also increasing time spent at higher intensity walking will elicit additional improvements in blood pressure relative to a message to only focus on increasing steps/day. The purpose of this paper is to present the rationale, study design, and protocols employed in WalkMore, a 3-arm 3-month blinded and randomized controlled trial (RCT) designed to compare the effects of two community pedometer-based walking interventions (reflecting these separate and combined messages) relative to a control group on blood pressure in sedentary/low active post-menopausal women, a population at increased risk of cardiovascular disease.

**Methods/Design:**

120 sedentary/low active post-menopausal women (45-74 years of age) will be randomly assigned (computer-generated) to 1 of 3 groups: A) 10,000 steps/day (with no guidance on walking intensity/speed/cadence; BASIC intervention, n = 50); B) 10,000 steps/day and at least 30 minutes in moderate intensity (i.e., a cadence of at least 100 steps/min; ENHANCED intervention, n = 50); or a Control group (n = 20). An important strength of the study is the strict control and quantification of the pedometer-based physical activity interventions. The primary outcome is systolic blood pressure. Secondary outcomes include diastolic blood pressure, anthropometric measurements, fasting blood glucose and insulin, flow mediated dilation, gait speed, and accelerometer-determined physical activity and sedentary behavior.

**Discussion:**

This study can make important contributions to our understanding of the relative benefits that walking volume and/or intensity may have on blood pressure in a population at risk of cardiovascular disease.

**Trial registration:**

ClinicalTrials.gov Record NCT01519583, January 18, 2012

## Background

Cardiovascular disease remains the leading cause of death in the U.S. [1]. and high blood pressure (hypertension) is one of the most common risk factors for both cardiovascular disease and stroke [2]. The prevalence of hypertension is positively associated with age [3], and is higher among men than women at younger ages, but these gender differences are reversed in older age [4]. At least part of the rise in blood pressure observed in later adulthood in women is related to menopause [5]. Increases in body mass index (BMI) account for some, but not all, of the observed increases in hypertension prevalence in adults; and thus an increasingly sedentary lifestyle has also been suggested as a contributory factor [6]. Based on objectively monitored behavior, less than 5% of the adult population obtains commonly recommended amounts (i.e., 30 minutes/day) of moderate-to-vigorous physical activity, with the lowest prevalence observed in women over 50 years old [7]. Even when intensity of activity is not considered, it is apparent that postmenopausal women are not very active. As a single illustrative example, traditional Amish women take 14,000 steps/day [8] whereas recent estimates indicate typical American women over 50 years of age take less than 5,000 steps/day [9-11]. Being female, older, and having a higher BMI were among the predictors of being classified as sedentary (i.e., taking less that 5,000 steps/day) based on objectively monitored data from the National Health and Nutrition Examination Survey (NHANES) [12]. Taking less than 7,500 steps/day is indicative of physical inactivity (i.e., not meeting public health recommendations for accumulating moderate or greater physical activity) [13] or otherwise being classified as “sedentary/low active ” [14].

Meta-analyses of walking exercise programs (i.e., focused on structured walking), [15,16] but also pedometer-based programs [17] (i.e., focused on lifestyle walking) reduce blood pressure. Studies of pedometer-based programs employing a step goal [17], and in particular a 10,000 steps/day goal [18], appear to have had the greatest impact on increasing physical activity. Attainment of this level is considered consistent with the physical activity levels of active individuals [14,19]. Moreau et al. [20] showed that increasing physical activity levels in hypertensive postmenopausal women from a baseline value of approximately 5,000 to 10,000 steps/day elicited a 6 mm Hg decrease in systolic blood pressure at 12 weeks and a further 5 mm Hg reduction at 24 weeks. Prudence dictates that any pedometer-determined steps/day goal be congruent with existing public health guidelines. Consistent evidence indicates that 30 minutes of at least moderate intensity physical activity is equivalent to 3,000-4,000 steps in adults [21,22]. Further, there is consistent support for a stepping rate (i.e., cadence) of 100 steps/minute to represent the lower bound of moderate intensity walking in adults [21,23-26], also producing 3,000 steps in 30 minutes (i.e., 100 steps/min * 30 minutes). To be considered a true translation of public health guidelines, at least 3,000-4,000 steps of any goal expressed as a total daily steps/day value should be of at least moderate intensity (i.e., be ≥100 steps/minute) [27].

The purpose of this paper is to present the rationale, study design, and protocols employed in WalkMore, a randomized controlled trial (RCT) designed to compare the impact of two pedometer-based walking interventions (BASIC vs. ENHANCED) relative to a control group on blood pressure in sedentary/low active post-menopausal women, a population at increased risk of cardiovascular disease.

## Methods/Design

### Trial design

WalkMore is a 3-month long trial with outcome measures at baseline and 3 months. The Principal Investigator and assessment staff are blinded to participants’ randomized allocation status. A biostatistician oversees the computer-generated program that will be used to randomly assign participants to 1 of 3 groups: A) 10,000 steps/day (with no intervention on walking intensity/speed/cadence; BASIC intervention, n = 50); B) 10,000 steps/day and at least 30 minutes in moderate intensity (i.e., at a cadence of at least 100 steps/min; ENHANCED intervention, n = 50); or a Control group (n = 20). The study was reviewed and approved by the Pennington Biomedical Research Center’s Institutional Review Board. The study is registered at ClinicalTrials.gov (Record NCT01519583) and it will be reported according to CONSORT guidelines [28].

### Participants and recruitment

We will recruit 120 participants for the WalkMore study. The Pennington Biomedical Research Center’s Recruiting Core will manage all participant recruitment activities (e.g., marketing, newspaper, billboards, email campaigns, health fairs, public speaking appearances, etc.). Potential participants responding to recruitment activities will be directed to a website and/or call center that is operated by 4 full-time recruiters. The core utilizes an electronic message tracking application that tracks webscreener and phone call activity, including a “smart” electronic web and phone screen system that facilitates screening potential participants upon initial contact and seamlessly matches them with an appropriate study, including WalkMore. A listserv was developed to manage email campaigns targeting the 12,000 subscribers who have opted to be notified of new studies via email. The core also has access to demographic information for approximately 25,000 participants who can be targeted for study recruitment, including WalkMore. Supplementary methods, including “snowballing techniques” that take advantage of current participants’ social networks will be included as the study is deployed.

### Screening and eligibility

We will employ an extensive screening process which we have found promotes adherence and excludes potential participants who cannot commit to the study. Web-based or telephone screening (≈ 15 minutes) will be used to identify potentially eligible participants based on sex (women), age (45-74 years), post-menopausal status (self-reporting at least 12 months since last menses), mobility (self-reporting physically capable of exercise), and performance of regular physical activity (yes/no). Potential participants identified at this stage will be invited to attend a 30-min group orientation session (scheduled in the early evenings once or twice a week, as numbers require) to learn more about the study, including randomization procedures, study requirements, personal risks and benefits, and participant rights. Potential participants who wish to continue with the screening process will be scheduled for the first of three subsequent screening visits and sent home with a copy of the study’s informed consent form to read over before their first screening visit.

Upon arrival at their first screening visit (SV1; ≈ 60 minutes), the study will be reviewed once more, all questions are answered, and participants will be asked to provide written informed consent prior to the administration of any of the following study procedures. A medical and health history will be obtained. Inclusion/exclusion criteria are summarized in Table 1. Participants reporting significant cardiovascular disease/disorders (including diabetes) or other significant medical conditions considered life-threatening or potentially interfering with or being aggravated by exercise, recently (with previous 6 weeks) donating blood or losing ≥20 kg in the previous year, having been hospitalized for mental illness within the previous 5 years, or planning to be out of the area for more than 3 weeks over the next 3 months will be excluded. Participants are further queried about their exercise habits to confirm eligibility (continues to self-report as not a regular exerciser). Blood pressure is taken and those with systolic pressure values of 130-179 mmHg or diastolic pressure values of 85-99 mmHg will be included. Participants taking blood pressure lowering medication and meeting the above criteria will still be eligible. Height, weight, and waist circumference are obtained; those with a BMI between 25-45 kg/m^2^ are included. Participants are then asked to wear a pedometer (NL-1000, NewLifestyles) and record their daily steps for one week before returning for their second screening visit (SV2).

**Table 1 T1:** Inclusion/exclusion criteria for women participating in WalkMore

**Inclusion criteria**	
Age	45-74 years
Post-menopausal status	Self-reporting at least 12 months since last menses
Mobility	Reporting physically capable of exercise (yes/no)
Physically inactive	Self-reported exercise behavior (yes/no)
Objectively determined sedentary	Average ≤5,000 steps/day during screening
Overweight/obese	Objectively verified BMI 25 – 45 kg/m^2^ OR waist circumference >88 cm [29]
Informed consent	The capability and willingness to give written informed consent, to understand exclusion criteria, and to accept the randomized group assignment are required.
Blood pressure	Systolic values of 130-179 mmHg or diastolic pressure values of 85-99 mmHg. Participants taking blood pressure lowering medication and meeting the above criteria are still eligible.

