**Exclusion criteria**	
Significant cardiovascular disease or disorders	Including but not limited to arrhythmias, myocarditis, cardiomyopathy, congestive heart failure, stroke or transient ischemic cerebral attacks, peripheral vascular disease with intermittent claudication, acute, chronic or recurrent thrombophlebitis
Other significant medical conditions	Including but not limited to diabetes, chronic or recurrent respiratory, gastrointestinal, neuromuscular, neurological, or psychiatric conditions. Musculoskeletal problems interfering with exercise. Immunodeficiency diseases or a positive HIV test. Malignancies in the past 5 years, with the exception of skin cancer therapeutically controlled. Any other medical condition or disease that is life-threatening or that can interfere with or be aggravated by exercise
Recent blood donation	Blood donation during the 6 weeks before the baseline evaluation (participants also will be asked to refrain from blood donation during study)
Large weight loss	20 or more kilograms in the past year
Other exclusions	Hospitalization for mental illness within the past 5 years. Plans to be out of the city more than 3 weeks over the next 3 months.

At SV2 (≈ 20 minutes), participants’ written records of their daily steps will be reviewed and compared to those recorded by the pedometer’s internal memory (not previously disclosed to participants). Those participants who wear the pedometer for at least 4 days and average < 7500 steps/day (defined as sedentary or low active [14]) will be asked to wear an accelerometer (GT3X+, ActiGraph LLC, Pensacola, FL) for one week before returning for their third and final screening visit (SV3, ≈ 30 minutes). At SV3, the participant’s accelerometer will be downloaded and reviewed for evidence of wearing compliance. Participants who wear the accelerometer for at least 4 days (≥ 10 hours each day), are willing to accept randomized group assignment, and remain committed to working through potential scheduling conflicts and other logistical issues that may come up during the intervention will be enrolled in the study and subsequently scheduled for baseline measures and randomization procedures. Participant’s accelerometer data collected during their screening process will serve as their baseline physical activity and sedentary behavior data.

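### The step-count inclusion limit has two values: at most 5,000 steps/day in Table 1, below 7,500 in the screening text

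*Protocol article*

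**What the plan says.** The article states the step-count criterion in two places.

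- **Table 1, inclusion criteria**, in the row for objectively determined sedentary status: "Average ≤5,000 steps/day during screening". No device and no minimum number of days are named.
- **Screening and eligibility, SV2 paragraph**: women with at least 4 days of pedometer wear go forward if they "average < 7500 steps/day (defined as sedentary or low active [14".

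The same section says of the table: "Inclusion/exclusion criteria are summarized in Table 1". At the third visit (SV3), "the participant’s accelerometer will be downloaded and reviewed for evidence of wearing compliance". Enrolment then depends on wear time, willingness and commitment: "Participants who wear the accelerometer for at least 4 days (≥ 10 hours each day), are willing to accept randomized group assignment".

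The Background defines both terms. Women are "classified as sedentary (i.e., taking less that 5,000 steps/day") at the lower limit, while "Taking less than 7,500 steps/day is indicative of physical inactivity" and is tied there to the label sedentary/low active. The Abstract and the purpose statement at the end of the Background use the wider label. The Discussion describes the study population as sedentary only.

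**The concern.** An inclusion criterion should give one answer for each woman screened. Here staff working from Table 1 would exclude women whom staff working from the SV2 text would enrol. Every enrolment between the two limits breaches one of the stated rules, and a reader of the results could not tell which population was meant.

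The limit also bears on the intervention itself. Both walking groups have the same 10,000 steps/day goal whatever their starting level, so the admissible baseline sets the rise that is asked for. The article supports its 6 mm Hg planning difference partly with a study in which raising activity "from a baseline value of approximately 5,000 to 10,000 steps/day elicited a 6 mm Hg decrease in systolic blood pressure at 12 weeks". How closely the enrolled women resemble that study's participants depends on which limit is applied.

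**Working it through.** No planned figure has to be reproduced. The check is a comparison of the texts plus one subtraction.

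**1. The two rules side by side**

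| Average steps/day in screening | Table 1 (≤5,000) | SV2 text (<7,500) |
|---|---|---|
| 5,000 or fewer | eligible | eligible |
| more than 5,000, fewer than 7,500 | **not eligible** | **eligible** |
| 7,500 or more | not eligible | not eligible |

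The populations are nested: every woman who meets Table 1 also passes SV2. The conflict is confined to the middle row.

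**2. Could these be successive stages?** They could if a later step applied 5,000. After SV2 comes the accelerometer week, and SV3 reviews those data for wear only. The enrolment conditions listed after SV3 contain no step limit. Table 1 is presented as a summary of the criteria, not as a further stage, so table and text should agree.

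**3. Could the two values describe one category loosely?** The Background separates them: under 5,000 is sedentary, and under 7,500 is sedentary/low active. Table 1 pairs its limit with the first term, and SV2 pairs its limit with the second. Each place is consistent with the definitions but not with the other place.

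**4. Which label does the rest of the article use?** Abstract and purpose statement: sedentary/low active, which fits 7,500. Discussion: sedentary, which fits 5,000. The wider label appears more often, but the article does not settle the question.

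**5. Rise needed to reach the goal**

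Rise = 10,000 − baseline; relative rise = rise / baseline.

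- At the Table 1 limit: 10,000 − 5,000 = 5,000 steps/day; 5,000 / 5,000 = 100%. Every woman eligible under Table 1 needs at least this.
- At the SV2 limit: 10,000 − 7,500 = 2,500 steps/day; 2,500 / 7,500 = 33%. A woman just below the limit needs just over 2,500.

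The smallest rise that the rules can ask for thus differs by a factor of two (5,000 / 2,500).

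**6. Can this be carried through to power?** That would need the share of women in the band, their mean baseline, and a relation between added steps and blood pressure change. The article gives none of these, so no power figure follows.

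**The case against.** The strongest defence is that the staged procedure is complete without the 5,000 limit, that the wider label recurs in the Abstract and purpose statement, and that one row of a summary table has merely fallen out of step. That is a plausible reading, and it limits the problem to a correctable inconsistency. It does not remove it: the row is an eligibility criterion, and the Discussion's wording supports the row. Treating Table 1 as the obvious outlier goes beyond the document.

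A second defence is that Table 1 names no device. Screening includes a pedometer week and an accelerometer week, so it is an inference, though a likely one, that both limits refer to the pedometer average. Even if Table 1 meant the accelerometer, the enrolment conditions apply no step limit to those data, so the conflict remains.

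A reader might also infer that the wider limit dilutes the 6 mm Hg effect in proportion to the smaller rise and leaves the control comparisons underpowered. The documents do not support this:

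- Nothing in them says that the blood pressure effect scales with added steps.
- The same scaling would credit women starting lower with more than 6 mm Hg. From 3,000, for example, it gives 6 × 7,000 / 5,000 = 8.4.
- The baseline of about 5,000 in the cited study appears to be a group average. A cohort admitted below 7,500 could have the same average, since the Background puts typical American women over 50 below 5,000.
- BASIC and ENHANCED share the limit and the step goal, so the argument does not separate those two arms.

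**Conclusion.** The contradiction stands and should be resolved before it governs enrolment. The same inclusion criterion has two values, 5,000 and 7,500 steps/day, with nothing in the article to reconcile them, and the population label varies along the same line. The conflict affects only women averaging above 5,000 and below 7,500. For them, it decides whether they may be randomized at all.

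Its known size is the width of that band and the difference in the minimum rise: at least 5,000 steps/day under one rule, possibly just over 2,500 under the other. This conclusion rests on the texts and needs no assumption about effect. Two stronger readings should not be drawn: that the trial has two separate target populations, since one is contained in the other, and that power is lost by any stated amount, since the share of women in the band is unknown.

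**What to change.** - Choose one step limit and state it identically in Table 1 and in the SV2 text. The choice is the sponsor's; this review does not say which limit is right.
- Bring the population label in the Abstract, purpose statement, Table 1 row and Discussion into line with that limit, using the Background's own definitions.
- In the Table 1 row, name the device and the minimum number of wear days to which the average applies.
- Apply the rule to every woman enrolled, and report how many women in each arm averaged between 5,000 and 7,500 steps/day at screening.

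The cost is a short amendment to one table row or one sentence, plus consistent wording elsewhere. The count needs no new data, because the screening step average is already recorded for each woman. The lower limit would narrow the recruitment pool. The higher one would admit women who need a smaller rise to reach the goal.

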**Exclusion criteria**	
Significant cardiovascular disease or disorders	Including but not limited to arrhythmias, myocarditis, cardiomyopathy, congestive heart failure, stroke or transient ischemic cerebral attacks, peripheral vascular disease with intermittent claudication, acute, chronic or recurrent thrombophlebitis
Other significant medical conditions	Including but not limited to diabetes, chronic or recurrent respiratory, gastrointestinal, neuromuscular, neurological, or psychiatric conditions. Musculoskeletal problems interfering with exercise. Immunodeficiency diseases or a positive HIV test. Malignancies in the past 5 years, with the exception of skin cancer therapeutically controlled. Any other medical condition or disease that is life-threatening or that can interfere with or be aggravated by exercise
Recent blood donation	Blood donation during the 6 weeks before the baseline evaluation (participants also will be asked to refrain from blood donation during study)
Large weight loss	20 or more kilograms in the past year
Other exclusions	Hospitalization for mental illness within the past 5 years. Plans to be out of the city more than 3 weeks over the next 3 months.

At SV2 (≈ 20 minutes), participants’ written records of their daily steps will be reviewed and compared to those recorded by the pedometer’s internal memory (not previously disclosed to participants). Those participants who wear the pedometer for at least 4 days and average < 7500 steps/day (defined as sedentary or low active [14]) will be asked to wear an accelerometer (GT3X+, ActiGraph LLC, Pensacola, FL) for one week before returning for their third and final screening visit (SV3, ≈ 30 minutes). At SV3, the participant’s accelerometer will be downloaded and reviewed for evidence of wearing compliance. Participants who wear the accelerometer for at least 4 days (≥ 10 hours each day), are willing to accept randomized group assignment, and remain committed to working through potential scheduling conflicts and other logistical issues that may come up during the intervention will be enrolled in the study and subsequently scheduled for baseline measures and randomization procedures. Participant’s accelerometer data collected during their screening process will serve as their baseline physical activity and sedentary behavior data.

